## Abstract

**Introduction:**

*Plasmodium knowlesi* has long been present in Malaysia, and is now an emerging cause of zoonotic human malaria. Cases have been confirmed throughout South-East Asia where the ranges of its natural macaque hosts and *Anopheles leucosphyrus* group vectors overlap. The majority of cases are from Eastern Malaysia, with increasing total public health notifications despite a concurrent reduction in *Plasmodium falciparum* and *P. vivax* malaria. The public health implications are concerning given *P. knowlesi* has the highest risk of severe and fatal disease of all *Plasmodium* spp in Malaysia. Current patterns of risk and disease vary based on vector type and competence, with individual exposure risks related to forest and forest-edge activities still poorly defined. Clustering of cases has not yet been systematically evaluated despite reports of peri-domestic transmission and known vector competence for human-to-human transmission.

**Methods and analysis:**

A population-based case–control study will be conducted over a 2-year period at two adjacent districts in north-west Sabah, Malaysia. Confirmed malaria cases presenting to the district hospital sites meeting relevant inclusion criteria will be requested to enrol. Three community controls matched to the same village as the case will be selected randomly. Study procedures will include blood sampling and administration of household and individual questionnaires to evaluate potential exposure risks associated with acquisition of *P. knowlesi* malaria. Secondary outcomes will include differences in exposure variables between *P. knowlesi* and other *Plasmodium* spp, risk of severe *P. knowlesi* malaria, and evaluation of *P. knowlesi* case clustering. Primary analysis will be per protocol, with adjusted ORs for exposure risks between cases and controls calculated using conditional multiple logistic regression models.

**Ethics:**

This study has been approved by the human research ethics committees of Malaysia, the Menzies School of Health Research, Australia, and the London School of Hygiene and Tropical Medicine, UK.

Strengths and limitations of this studyThis study design will allow identification of *Plasmodium knowlesi* malaria risk factors, at-risk groups and case clustering, while controlling for the large number of human exposure variables related to complex monkey host and mosquito vector transmission dynamics.As *P. knowlesi* malaria can be acquired by all demographics, the selection of community controls allows extrapolation of exposure variables to the true population at risk, and will help to guide future public health strategies for human *P. knowlesi* malaria throughout the region.While potential bias in selecting community controls does exist by assuming all cases have the same access to the district hospital referral and enrolment site, this is minimised by standard Malaysian Ministry of Health malaria health policies.Controls matched to the same village as the case, who have lived there over the same preceding time period, will allow delineation of microepidemiological risk exposures on an individual and household level and will also assist in minimising bias related to differences in case accessibility to the enrolment sites.Not matching controls to the case's age and gender gives less power to detect differences in other individual exposure risks within these demographics; however, it does allow analysis of these as potential independent risk factors, including their relationship with disease severity.

## Introduction

### *Plasmodium knowlesi* as an emerging public health problem in Malaysia

The first naturally acquired human infection of the simian malaria parasite *Plasmodium knowlesi* was reported in 1965 in Pahang, Peninsular Malaysia.^1^ A survey of 1117 people living in the vicinity of the case failed to produce further evidence of *P. knowlesi* human infection.^2^ Subsequent screening for *P. knowlesi* was limited due to the assumed scarcity of zoonotic human malaria and an inability to differentiate morphologically between *P. knowlesi* and *P. malariae* using routine microscopy.^3^
^4^ In 2004, atypical *P. malariae* microscopy reported cases were correctly identified by PCR as a substantial focus of human *P. knowlesi* infections at Kapit in Sarawak, Eastern Malaysia.^5^
*P. knowlesi* is also commonly misreported by microscopy as either *P. falciparum* or *P. vivax* in endemic areas such as Sabah, Malaysia,^4^
^6^ where state guidelines currently only require routine referral of microscopic *P. malariae* cases for confirmatory PCR speciation.^7^

Current evidence suggests that *P. knowlesi* has long been present in Eastern Malaysia.^6^
^8^
^9^ Analysis of *P. knowlesi* mtDNA sequences from Sarawak suggest that *P. knowlesi* was present in local macaques before the arrival of humans in South-East Asia^10^ and a large increase in the parasite population corresponds to the initial rise in the human population in this region around 30 000–40 000 years ago.^11^ The earliest PCR confirmation of *P. knowlesi* comes from archival slides from Sarawak (originally diagnosed as *P. malariae*) dating back to 1996.^12^ Recent studies in Eastern Malaysia have consistently shown that only a very small proportion (<1%) of *P. malariae* cases diagnosed by microscopy can be confirmed by PCR. The vast majority of these cases are, in fact, *P. knowlesi*.^5^
^8^
^13–17^ By extension it is possible that a significant proportion of *P. malariae* cases reported historically in Eastern Malaysia were, in reality, *P. knowlesi* infections. The earliest malaria surveys conducted in Tambunan, Sabah, between 1939 and 1942 described high-intensity malaria foci in hilly ravines with unconfirmed *P. malariae*.^18^ In Sarawak, results from the first recorded microscopy-based surveys conducted in 1952 indicated that *P. malariae* accounted for 33% of all malaria cases and up to 76% in some areas.^2^

In Sabah, recently, a marked, rapid increase in the number of *P. knowlesi* cases beginning in the south-west and progressing north-easterly has been reported.^19^ Public health microscopy notifications for *P. knowlesi* in Sabah (including those reported as *P. malariae*) have increased from around 2% (59/2741) of all malaria cases in 2004, to 35% (703/1936) in 2011^19^ and, recently, to 62% in 2013 (996/1606) (Sabah Department of Health, unpublished). The rise in *P. knowlesi* notifications in Sabah may also be underestimated given PCR-confirmed *P. knowlesi* is misdiagnosed as *P. falciparum* or *P. vivax* in up to 13% and 10% of cases, respectively, by routine microscopic examination in this area.^4^ In Sarawak, government health reports of *P. knowlesi* or *P. malariae* microscopy notifications totalled 14.3% (1731/12 082) of all malaria cases between 2000 and 2006,^9^ increasing to 41% (897/2189) in 2009^15^ and to 73% (737/1004) in 2013.^20^ The change in *Plasmodium* spp proportions in both Sabah and Sarawak coincides with an effective national Malaria Control Program implemented in Eastern Malaysia in 1971,^21^ with a consequent decrease in *P. falciparum* and *P. vivax* cases.^19^ However, this does not explain the differences in transmission dynamics that have resulted in a marked increase in absolute numbers of *P. knowlesi* cases in Sabah but not in Sarawak.

Since 2004, sporadic cases of PCR-confirmed *P. knowlesi* human malaria have also been reported in Peninsular Malaysia and a number of Asian countries including Thailand, Vietnam, Cambodia, Myanmar, Singapore, Brunei, Indonesia, India, China and the Philippines.^8^
^22–30^ Recent risk maps suggest that large areas in this region have the necessary pre-requisites for an infectious *P. knowlesi* reservoir^31^ and as molecular diagnosis is not routine outside Malaysia, it is possible that a substantial number of *P. knowlesi* infections are going undetected. However, existing evidence also suggests that *P. knowlesi* incidence is relatively low in areas where other human *Plasmodium* spp predominate.^23^
^32^ Outside Malaysia, *P. knowlesi* occurs most commonly within mixed infections^23^
^27^
^33^ and has not yet been shown to cause severe disease. In Malaysia, by contrast, *P. knowlesi* is associated with a threefold risk of severe disease compared with *P. falciparum*^17^ and fatal outcomes have been reported.^34^
^35^

### Current understanding on epidemiological patterns of *P. knowlesi* risk

Currently it is unclear why patterns of *P. knowlesi* infection and disease in at-risk populations vary so markedly across this region. Overall, the distribution of cases is constrained by the ranges of the predominant natural hosts for *P. knowlesi*: long-tailed (*Macaca fascicularis*) and pig-tailed (*M. nemestrina*) macaques.^36^ Transmission also depends on the presence of competent mosquito vectors within the *Anopheles leucosphyrus* group,^37^ which, together with factors that determine the nature of vector-human contact, results in a spatially heterogeneous pattern of *P. knowlesi* transmission and more fundamental variations in the epidemiology of the disease. In Kapit, Sarawak, for example, *A. leucosphyrus* (previously described as *A. latens*) was identified in 2006 as a *P. knowlesi* vector of both humans and monkeys and demonstrated relatively high human biting rates within a farming area at the forest fringe.^38^ These entomological findings were consistent with results from an epidemiological study carried out at Kapit Hospital in 2006–2008, during which 87% (93/107) of patients who were prospectively admitted with *P. knowlesi* malaria reported having engaged in recent undefined forest or forest-edge activities.^39^ The epidemiological picture in Sabah, where *Anopheles balabacensis* (the vector used in human *P. knowlesi* transmission studies in the 1960s^40^) is assumed to be the main vector for *P. knowlesi*,^41^
^42^ is hypothesised to be different. However, a prospective study of malaria patients from a referral catchment area of north-western Sabah also described 92% (119/130) of PCR confirmed *P. knowlesi* malaria cases having forest or plantation exposure. Despite this, patients with *P. knowlesi* in this study were no more likely than patients with *P. falciparum* to report staying overnight or spending >4 h in a forest or plantation in the previous 1 month.^17^ In contrast, living within a 20 min walk of unclassified forest type or a plantation did appear related (p=0.001 and 0.015, respectively), in addition to a positive history of sighting a monkey in the previous 4 weeks (p<0.001).^17^

While comparisons in *P. knowlesi* transmission patterns between Sabah and Sarawak remain difficult given broad definitions of forest and forest-edge exposure in previous studies, differences in more specific related factors may be impacting on the patterns of clustering of *P. knowlesi* cases. Initial studies from Sarawak had shown a higher prevalence of *P. knowlesi* malaria in adult males with occupational forest exposure, with no clustering of cases despite the fact that most people live in communal longhouses.^5^ Data from Sabah have also documented up to 78% of *P. knowlesi* cases are male^17^
^19^ while for female cases a bimodal age distribution was described, which may still indicate that risk of infection is predominantly linked to exposure activities.^19^ In addition, no relationship with occupation was seen when comparing *P. knowlesi* with *P. falciparum* cases.^17^
^19^ However, a study at Kudat at the north-western tip of Sabah showed clear differences to Sarawak with both a wide age distribution of cases and contemporaneous family clusters including children and town residents, suggesting peridomestic transmission is also occurring.^43^
*P. knowlesi* cases in Sabah have also been shown to demonstrate temporal clustering, with marked seasonality (p<0.001) associated with a peak of cases in May and 3–5 months post-high rainfall.^19^
^43^

Evidence of peridomestic transmission in Sabah raises the possibility of human-to-human transmission. To date, this is not evident from focused studies outside Sabah where macaque and human samples have been compared. These include the analysis of *P. knowlesi* CSP or MSP gene sequences in Sarawak and Peninsular Malaysia, and also in other countries including Singapore and Thailand, which all showed a large number of shared haplotypes that were similarly diverse in both hosts, supporting a zoonotic rather than exclusively human transmission mode.^10^
^32^
^44^
^45^ In addition, no evidence of ongoing human *P. knowlesi* transmission in areas without a macaque reservoir has been documented. However, in the absence of large-scale molecular studies comparing humans and macaques in this region, and given human-to-human transmission has been demonstrated under experimental conditions,^40^ the occurrence of natural human-to-human *P. knowlesi* transmission alongside monkey-to-human transmission remains possible.

### Key knowledge gaps in epidemiological determinants of *P. knowlesi* risk

*P. knowlesi* acquisition risk factors related to behaviour or environment currently remain poorly defined even in the more intensively studied areas of Eastern Malaysia. Changes in land use such as shifts in agricultural practices, deforestation and forest fragmentation have been proposed as key drivers in the emergence of *P. knowlesi* infection.^8^ However, there has been no detailed evaluation of potential risk factors related to household characteristics or local patterns of land use/land cover. In addition, there is limited understanding of human movement patterns or travel history related to differences in forest or forest edge exposure, including duration, frequency and timing of activities. Occupational exposure has not been evaluated in a systematic manner, either with respect to seasonal practices or differences associated with rubber or palm oil plantations versus traditional freeholder farming. To date, no studies have looked in detail at human and monkey interaction, considering the zoonotic transmission mode of *P. knowlesi* and the potential novel risks related to encroachment of humans on macaque habitats and vice versa. This interaction could relate to proximity of vectors and include conflict around availability of food for macaques from human agricultural practices such as cultivated fruit orchards, rice paddies or cornfields, in addition to traditional or changing practices such as trapping or hunting monkeys for pets or food.

Current reported studies have not been designed to control for other human behavioural or immunological factors such as the documented higher incidence of *P. knowlesi* malaria in older age^17^
^39^
^43^
^46^ or the risk of *P. knowlesi* malaria during pregnancy. Age as a demographic factor alone also needs investigation, given widespread reports of *P. knowlesi* cases in children in Malaysia and elsewhere in South-East Asia.^23^
^46^
^47^ In addition, no studies have evaluated whether genetic factors affect individual *P. knowlesi* malaria acquisition risk, such as seen with the protective nature of certain human red blood cell polymorphisms against other *Plasmodium* spp.^48–50^

### Case–control study designs to identify risk factors for malaria

Case–control study designs have been used in areas of low endemicity in the past to identify risk factors for malaria due to other *Plasmodium* spp.^51^ Existing efforts to fill knowledge gaps in individual risk for human *P. knowlesi* malaria focus on delineating activities at the forest edge and within the forest, and differentiating these in terms of occupational risk and those related to domestic behaviour. As the current incidence of *P. knowlesi* malaria in Sabah is relatively low, a prospective cohort study design would not be an efficient way of assessing these relative risks because of the very large number of participants that would need to be recruited. In addition, with a cohort study the loss to follow-up of any participants would negatively impact the causal analysis of the primary outcome of interest, which is the acquisition of *P. knowlesi* malaria. The case–control design is also particularly well suited in identifying at-risk groups or clustering at a finer epidemiological scale as it allows controlling for the complex and large number of human exposure variables involved in the transmission dynamics of *P. knowlesi* infection. In addition, this design is useful for generating hypotheses on *P. knowlesi* acquisition that can be tested using other future study designs such as cross-sectional surveys, which are more suited to providing detailed information on population-wide *P. knowlesi* prevalence including asymptomatic infection.

## Aim and objectives

The study design described in this protocol will allow evaluation of the primary research question: “Which factors lead to increased risk of acquiring human *P. knowlesi* malaria in Sabah, Malaysia?” Secondary objectives will include comparisons of malaria acquisition risk between different *Plasmodium* spp, risk of severe disease within the *P. knowlesi* group of malaria cases, and evaluation of *P. knowlesi* clustering.

Information resulting from this study will assist in guiding public health strategies for malaria in this region and provide valuable human epidemiological data for integration with concurrent studies on the entomology, primatology and land use aspects of *P. knowlesi* transmission (Monkeybar project: UK MRC ESEI Grant #G1100796) and the clinical treatment of *P. knowlesi* malaria (clinicaltrials.gov #NCT01708876).

## Methods and analysis

*Current status*: Enrolment started in December 2012, with 189 *P. knowlesi* cases and 564 community controls as on June 2014.

### Study design

This will be a population-based case–control study conducted in two adjacent districts: Kudat and Kota Marudu in the state of Sabah, Malaysian Borneo (figure 1). Within the study sites, all malaria cases, regardless of parasite species, meeting specified inclusion criteria will be enrolled at the corresponding district referral hospital over a 2-year period. Research fieldworkers will go to the village of the case within 2 weeks of focal case detection and randomly select three community controls who have primarily resided in the village for the past 3 weeks. This will enable matching of the controls with the case by the same geographical area (local village) and preceding minimum time period of exposure risk (3 weeks).

**Figure 1 BMJOPEN2014006004F1:**
[figure not shown]
Map of study sites.

#### Study sites

Kudat and Kota Murudu districts cover an area of 3204 km^2^ over the north-western tip of the state of Sabah, Malaysian Borneo and have a combined population of around 150 000 (2010 data^52^). These sites were chosen predominantly because of documented high incidence of *P. knowlesi* infection; in particular with *P. knowlesi* being the predominant species in Kudat.^43^
^46^ Kudat and Kota Murudu districts have central referral hospitals serving defined catchment areas with large outpatient and inpatient facilities. Recruitment was also expanded to include patients presenting primarily to Kota Marudu District Hospital from the neighbouring Pitas district, with a higher proportion of cases due to other *Plasmodium* spp enabling secondary objectives to be evaluated.

#### Community controls

Because *P. knowlesi* can be acquired by either sex and at any age,^34^
^39^
^43^
^46^ community controls can provide an accurate representation of the study base population. This enables extrapolation of explored variables to the true population at risk.^53^ Choosing controls with no history of fever minimises possible confounding from any concurrent acute illness. By not choosing hospital controls there is some bias generated in assuming controls enrolled out in the community have the same access to the hospital study site as cases. The choice of community controls may also create bias by assuming that the malaria cases that present to the hospital and are enrolled genuinely account for all malaria cases in the community, that is, the study base population. However, in the current setting, factors that increase the likelihood of ascertaining all cases include (1) mandatory state reporting and hospital referral of malaria cases from government and private clinics; (2) the presence of only a single district referral hospital in each of the two study sites and (3) the provision of free or relatively inexpensive treatment at government health facilities. State Ministry of Health guidelines also dictate that a blood film for malaria should be prepared routinely for any patient who presents to a government health facility with fever.

#### Matching controls to the case's home village

This further minimises case ascertainment bias related to variations in geographical accessibility to the main referral study site. Matched village controls may reside anywhere within the study districts, whereas hospital controls may potentially come from a more restricted geographical area around the hospital. This design also provides greater statistical power to evaluate microepidemiological features related to individual and household factors. This was deemed more important than a design using hospital controls, which would have enabled comparisons between different locations and villages, but which would have had less power to delineate individual behaviour and demographic exposure risks.

#### Matching controls for preceding time exposure

Controls will be enrolled within a 2-week time period following identification of the case. Only individuals who have resided in the study area over a 3-week period prior to the presentation of the matched case will be eligible. This will encompass the prepatent time period of *P. knowlesi* infection of around 9–12 days.^40^ Analysis of potential relationships that vary over time such as seasonal planting or harvesting, other agricultural practices, cultural events or meteorological data will be possible.

#### Non-matching controls for age/gender

While this would have given additional power to detect differences in exposure risks within these demographics, it was decided that age and gender should be evaluated as potential independent risk factors. This will also allow comparisons between *Plasmodium* spp and with disease severity related to age or gender.

#### Recruitment/sample size

We aim to recruit all cases of confirmed malaria of any species or severity over the study duration from Kudat and Kota Murudu district hospitals. On the basis of current recruitment rates of around 10 malaria cases per month over the last year from both sites, we expect to enrol approximately 240 cases of *P. knowlesi* malaria and an additional 90 cases of malaria due to other species in the period December 2012 to December 2014. For the 330 malaria cases we will recruit 990 matched controls. A recruitment logbook will be kept for all screened cases and controls to document reasons for non-eligibility, which will be included in the analysis. With three controls per case, assuming probability of exposure among controls (Po) is 0.1, and the relative risk (RR) of acquiring *P. knowlesi* malaria in exposed subjects relative to unexposed subjects is 0.3, we will need to study a minimum of 210 *P. knowlesi* cases to be able to reject the null hypothesis that there is no difference between cases and controls (ie, relative risk=1), with 80% power and an α level of 0.05.^54^

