#### Definition and selection of community controls

A systematic selection procedure will be used to recruit three community controls for each case matched to the same village. This number of controls was chosen to provide sufficient statistical power to measure exposure effects, while at the same time making the recruitment process feasible logistically. Selection of control households and individuals within these households will be conducted using a validated and pretested random method based on up-to-date Malaysian Public Health Department village maps and household lists. Corroboration of the number of households will be undertaken with local residents, public health officers and village heads, where available. Households will be numbered using either the map and/or the household head of family name. A smartphone application generates a random number corresponding to one of the households. Individuals primarily residing within the selected household in the previous 3 weeks will be numbered and then randomised by the same application. All households within the village and all individuals within that household will have an equal chance of being selected. If the selected individual is not present when the fieldworkers visit the household, then they will return up to three times, which may include an arranged later time on the same day or on subsequent days. This will minimise selection bias related to the higher likelihood of male adults or school age children not being present at the household during the day. If it is not possible to obtain informed consent from a selected individual or if the specified inclusion criteria are not met, another individual within the same house will be selected based on the next randomly generated number. Failing this an alternative household will be selected using the same method.

*Control inclusion criteria:* Appropriate informed consent obtained; agree to finger-prick blood sample; negative blood slide and PCR result for malaria (delayed); primarily resided in the study area in preceding 3 weeks; residence can be located and mapped; no history of fever in previous 48 h.

*Control exclusion criteria:* Previously recruited as a case; previously recruited as a control; member of a previously selected control household; age<4 weeks.

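### The stated minimum of 210 cases does not follow from the printed inputs, and the only power example is for a protective exposure

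*Protocol article*

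**What the plan says.** The protocol article's section Recruitment/sample size contains the study's only power statement. Its inputs are "With three controls per case, assuming probability of exposure among controls (Po) is 0.1", a relative risk of acquiring *P. knowlesi* malaria that "in exposed subjects relative to unexposed subjects is 0.3", and a test "with 80% power and an α level of 0.05". Its result is that "we will need to study a minimum of 210" *P. knowlesi* cases. The paragraph cites a reference for the method, but states neither the sidedness of the test nor the correlation of exposure within matched sets. The same section expects about 240 *P. knowlesi* cases over the recruitment period.

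The section Definition and selection of community controls confirms the design: the procedure is to "recruit three community controls for each case matched to the same village". The section Aim and objectives gives the primary question as "Which factors lead to increased risk of acquiring human" *P. knowlesi* malaria in Sabah.

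**The concern.** Two things do not fit.

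- The paragraph prints a full set of inputs and a result, and the result looks too large for three controls per case.
- The relative risk is defined as exposed relative to unexposed, so 0.3 describes an exposure that removes 70% of the risk. The primary question concerns exposures that raise it.

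At stake is what a reader can learn about the study's sensitivity. If the inputs and result disagree, the stated 80% power is not the power of this design. If the example points in the other direction, the reader cannot invert it to find the smallest risk factor the study could be expected to detect.

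**Working it through.** **Inputs.** From Recruitment/sample size: M = 3 controls per case, p0 = 0.10, effect 0.3, power 80%, alpha 0.05. My assumptions: two-sided test (z = 1.960 and 0.8416), effect read as an OR, and phi between 0 and 0.3 because none is stated.

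Exposure among cases: p1 = 0.3×0.10 / (0.90 + 0.3×0.10) = 0.0323. Difference p0 − p1 = 0.0677, squared 0.004589.

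**Unmatched formula.** n = [1.960·√((1+1/M)·p̄(1−p̄)) + 0.8416·√(p1q1 + p0q0/M)]² / (p1−p0)², with q = 1 − p and p̄ = (p1 + M·p0)/(1+M).

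- M = 3: p̄ = 0.0831; n = (0.6246 + 0.2082)² / 0.004589 = **151.1**.
- M = 1: p̄ = 0.0661; n = (0.6888 + 0.2930)² / 0.004589 = **210.07**.

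Other three-control variants also miss 210: continuity-corrected 171, 0.3 taken as a plain ratio of exposure proportions 140, one-sided 117, unpooled variance 105, single pooled variance 174.

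**Matched formula (conditional score test for 1:M sets).** Let T_k be the probability term for a set with k exposed members, and ψ the OR. Then e_ψ = Σ kT_kψ/(kψ+M−k+1), v_ψ = Σ kT_kψ(M−k+1)/(kψ+M−k+1)², and n = (0.8416·√v_ψ + 1.960·√v_1)² / (e_1−e_ψ)².

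For M = 3, ψ = 0.3, phi = 0: T_1 to T_3 = 0.2587, 0.0340, 0.0018; e_1 = 0.0830, e_ψ = 0.0322, v_1 = 0.0573, v_ψ = 0.0279. So n = (0.1405 + 0.4693)² / 0.0508² ≈ **144.1**.

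| phi | cases needed, OR 0.3, M = 3 | power at 210 sets, OR 0.3 | cases needed, OR 3.33, M = 3 | cases needed, OR 0.3, M = 1 |
|---|---|---|---|---|
| 0 | 144.1 | 94.5% | 47.0 | 195 |
| 0.1 | 146.9 | 93.9% | 51.7 | 213 |
| 0.2 | 152.7 | 92.7% | 57.9 | 235 |
| 0.3 | 162.9 | 90.7% | 66.1 | 261 |

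**What does give 210?** I found three routes, each needing an input other than those printed, or one left unstated:

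- one control per case, unmatched and uncorrected, OR 0.3: 210.07;
- three matched controls, OR 2.0, phi 0.2: 209.8;
- three matched controls, OR 0.3, phi about 0.5: 210.8. The largest phi possible with these margins is √(p1q0/(q1p0)) = √0.3 = 0.548, so this is close to the ceiling.

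**Power in the direction of the question.** With p0 = 0.10 and three matched controls, 80% power is reached at these ORs:

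- 210 sets: 1.90 (phi 0) to 2.00 (phi 0.2);
- 240 sets: 1.83 (phi 0) to 1.92 (phi 0.2).

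**The case against.** **The figure might be right under an unstated phi.** The method is cited rather than shown, and a condensed article may leave phi to the full protocol. That keeps 210 from being impossible for three matched controls. It needs a correlation near the mathematical limit, however, and a reader of the paragraph cannot know that.

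**The cause is not established.** A reader might infer from the 210.07 that the authors forgot the 1:3 ratio. The documents do not support that. The match depends on one variant, the unmatched uncorrected formula with an OR. The matched 1:1 formula gives 195 to 261 for phi 0 to 0.3, and a plain ratio gives about 194. Three matched controls with OR 2.0 and phi 0.2 fit equally well, and there the printed effect size would be the error. This objection stands.

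**A protective example is legitimate.** The primary exposures in the Statistical plan include red blood cell polymorphisms, which the introduction motivates by their protective role against other species, and the Household survey records malaria prevention methods. At 10% exposure an OR of 0.3 is also the more demanding case: 144 to 163 sets against 47 to 66 for 3.33. This stands in part, so the direction mismatch is secondary. It still leaves most of the demographic, behavioural and socioeconomic exposures without a relevant power statement.

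**Little depends on 210.** The study aims to enrol every eligible case in a fixed period, and the discrepancy errs towards more power for the printed scenario. This also stands.

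**Conclusion.** The point holds as an internal inconsistency: the minimum of 210 does not follow from the printed inputs. They imply about 151 cases unmatched, or 144 to 163 matched for phi 0 to 0.3. At 210 sets the matched formula gives about 91–95% power for the stated effect. This rests on a two-sided test, the effect read as an OR, and phi no larger than 0.3. Which input is at fault cannot be settled from the article.

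The example also runs against the direction of the primary question, and the two directions are not interchangeable at 10% exposure.

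Two stronger readings are not supported. The study is not underpowered for its printed scenario. Nor would a null result for a risk factor be uninterpretable, because the Statistical plan commits to ORs with 95% confidence intervals, which show the effects that the data exclude.

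**What to change.** Revise the one paragraph in Recruitment/sample size:

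- Return to the original calculation and reconcile the effect size, the control ratio and the within-set correlation with 210. Do not simply replace 210 by a smaller number, since the printed effect may itself be the misprint.
- State phi and the sidedness of the test.
- Give the power in the direction of the question. For example, at 10% exposure with three matched controls, 210 sets give 80% power for an OR of about 1.9 (phi 0) to 2.0 (phi 0.2), and the expected 240 sets for about 1.83 to 1.92.
- If OR 0.3 is kept as a protective example, give the roughly 144 to 163 cases it needs for phi 0 to 0.3.

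The cost is rewording and one recalculation. The recruitment target, matching and analysis are unchanged.
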